## Abstract

Background: Chronic pelvic toxicity induced by radiotherapy and/or chemotherapy (R/CIPT) is a debilitating sequela in gynecological cancer survivors, often refractory to conventional treatments and potentially linked to gut microbiota dysbiosis. Ozone therapy (OT), particularly rectal insufflation, demonstrates anti-inflammatory and redox-modulating effects through hormetic mechanisms (Nrf2 activation/NF-κB inhibition). We hypothesize that its clinical benefit is mediated, in part, by restoring gut microbial homeostasis. Objective: This manuscript proposes a clinical study to evaluate the impact of rectal OT on the gut microbiota of patients with gynecological cancers and chronic R/CIPT. Proposed Methods: A prospective, observational study of 38 patients is outlined: 19 with CTCAE v5.0 Grade ≥2 chronic R/CIPT receiving compassionate rectal OT (~40 sessions over 4 months), and 19 matched controls without toxicity. Stool samples for 16S rRNA sequencing will be collected from the OT group pre- and post-intervention and once from controls. Primary endpoints are changes in microbiota composition/diversity and pelvic toxicity scores (CTCAE v5.0, EORTC QLQ-CX24). Secondary endpoints include quality of life (EORTC QLQ-C30, EQ-5D-5L), anxiety/depression (HADS), and serum inflammatory/oxidative stress biomarker analysis. Anticipated Results and Conclusion: This will be the first study to prospectively investigate whether rectal OT’s effect correlates with a beneficial shift in the gut microbiota, specifically an increase in commensals (e.g., short-chain fatty acids producers) and a decrease in pathobionts. If successful, OT could be assessed as a novel, microbiota-targeting intervention for R/CIPT. The findings from this pilot study will provide the necessary groundwork for a future randomized controlled trial to definitively establish causality and efficacy.

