## 5. Proposed Clinical Study/Protocol

Study Population. Primary Cohort (Group R/CIPT, Radiotherapy/Chemotherapy-Induced Pelvic Toxicity): Adult women (≥18 years) with gynecological malignancies (cervical, endometrial, vulvar, vaginal) who have received pelvic RT with/without CT and present with chronic pelvic toxicity (≥3 months duration) rated as Grade ≥2 according to the Common Terminology Criteria for Adverse Events (CTCAE) v5.0 from the U.S. National Cancer Institute. In our institution, these patients are usually referred for compassionate OT due to symptoms refractory to conventional treatment. Control Cohort: Gynecological cancer patients matched by age (±5 years) and primary tumor location, treated with R/CIPT but without symptoms of pelvic toxicity.

Intervention: Rectal Ozone Insufflation +/− direct local application to the affected mucosa (rectal, vesical, and/or vaginal), based on the standard treatment protocol of the Chronic Pain Unit for compassionate use of OT. Proposed Regimen: It usually consists of 40 sessions administered over 4 months, following the unit’s standard operating procedures. The ozone concentration (µgO_3_/mLO_2_) will start at 10 µg/mL and increase by 5 µg/mL every 2 sessions until it reaches 30 µg/mL by the 9th session, after which it will be maintained until week 16. The volume will start at 180 mL and will be progressively increased to 300 mL if tolerated. The total ozone dose will range from 1800 µg to 9000 µg. To address standardization, the rectal ozone insufflation procedure will use a sterile, flexible catheter (14–16 Fr, 20–25 cm), inserted 7.5–12 cm into the rectum after lubrication. The patient will be positioned on their side, and the oxygen-ozone mixture will be administered over 5 min. All procedures will follow the unit’s standard operating protocols and be performed by trained staff. This approach is supported by published clinical protocols and safety data [51].

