Inclusion Criteria for all study participants: (1) Adult women (≥18 years of age) with a histologically confirmed gynecological malignancy (cervical, endometrial, vulvar, or vaginal), of any stage, who have completed a course of pelvic RT and/or CT. (2) Ability to understand and willingness to sign the study-specific Informed Consent Form. Additional criteria for inclusion in the OT Group: Presence of chronic R/CIPT, with a duration of ≥3 months following conventional symptomatic management. A toxicity grade of 2 (moderate symptoms; limiting instrumental activities of daily living) or higher, as per the CTCAE v5.0.

Exclusion Criteria for all study participants: any of the following will preclude inclusion: (1) Failure to meet all the inclusion criteria specified above. (2) Unwillingness or inability to provide written informed consent for study participation. (3) Presence of active inflammatory bowel disease (e.g., Crohn’s Disease, Ulcerative Colitis) or a history of major gastrointestinal resection (excluding appendectomy) that could significantly alter gut anatomy and microbiota. (4) Any uncontrolled intercurrent illness or psychiatric condition that, in the investigator’s opinion, would limit compliance with study requirements or interfere with the interpretation of results.

Withdrawal Criteria. Participants will be withdrawn from the study under the following circumstances: (1) Voluntary Withdrawal: At the patient’s own request, at any time and for any reason, without any penalty or impact on their future clinical care. (2) Loss to Follow-up: Inability to contact the patient or their failure to attend scheduled study visits. (3) Clinical Decision: Withdrawal by the principal investigator due to the occurrence of an adverse event, intercurrent illness, or any other clinical reason that justifies discontinuation for the patient’s well-being or the integrity of the study. (4) Protocol Violation: Significant deviation from the study protocol.

All patients, regardless of their decision to participate, decline, or withdraw from the study, will continue to receive standard oncological care and follow-up from their treating physicians. Withdrawal from the study will not affect their access to routine or compassionate medical treatments, including ozone therapy if clinically indicated.

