## Figures and Tables

**Figure 1 jcm-14-08015-f001:**
[figure not shown]
Proposed Mechanisms of Rectal Ozone Insufflation in Modulating the Gut Microbiome and Restoring Intestinal Homeostasis. This schematic illustrates the hypothesized pathway through which medical ozone, administered via rectal insufflation, exerts its effects. The core principle is oxidative hormesis, where controlled, low-dose ozone triggers a beneficial adaptive response. The process begins with (1) the local application of ozone in the gut lumen, which induces a mild, transient oxidative stress. This primary event initiates two key parallel mechanisms: (2) the Direct Modulation of the Gut Microbiota, and (3) the Activation of Host Cellular Pathways (Nrf2/SIRT1). These mechanisms converge to (4) Improve Gut Barrier Integrity and (5) Reduce Local and Systemic Inflammation, ultimately leading to the restoration of a healthy gut ecosystem and amelioration of disease symptoms. HO-1: Heme Oxygenase-1; IL-1β: Interleukin-1 beta; IL-6: Interleukin-6; IL-10: Interleukin-10; NF-κB: Nuclear Factor Kappa-Light-Chain-Enhancer of Activated B cells; NLRP3: NLR Family Pyrin Domain Containing 3; Nrf2: Nuclear Factor Erythroid 2–Related Factor 2. QT, Chemotherapy; RT, Radiotherapy; SCFAs: Short-Chain Fatty Acids; SIRT1: Sirtuin 1. TMAO: Trimethylamine N-Oxide; ↑, increase; ↓, Decrease.

**Table 1 jcm-14-08015-t001:** Schematic of the Rectal Ozone Therapy (OT) Clinical Study Design.

Stage	Key Elements	Study Groups & Sampling	Method and Endpoints
Population & Criteria	Objective: Adult women (≥18 years) with gynecological malignancy who have completed pelvic radiotherapy (± chemotherapy).	R/CIPT + OT Group (*n* = 19): With chronic pelvic toxicity (CTCAE ≥ Grade 2, ≥3 months duration). Control Cohort (*n* = 19): No pelvic toxicity, matched by age and tumor site.	Inclusion/Exclusion Criteria: Ensuring exclusion of confounding factors (e.g., active inflammatory bowel disease).
Intervention & Treatment	Intervention: Ozone Therapy (OT) via rectal insufflation with/without direct local application.	OT Group Only: Receives ≈ 40 sessions of OT over 4 months.	Ozone Regimen: Progressive dosing (10 µg/mL up to 30 µg/mL).

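### Eligibility contradicts itself on whether pelvic radiotherapy is required, so chemotherapy-only controls may enter the toxicity-versus-control comparison

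*Protocol article*

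**What the plan says.** The protocol article describes required prior treatment in four places.

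- **Section 5, inclusion criteria.** Under the label "Inclusion Criteria for all study participants", criterion 1 admits women "who have completed a course of pelvic RT and/or CT".
- **Section 5, Study Population, primary (toxicity) cohort.** Patients are those "who have received pelvic RT with/without CT and present with chronic pelvic toxicity".
- **Section 5, Study Population, control cohort.** Controls are "matched by age (±5 years) and primary tumor location" and were "treated with R/CIPT but without symptoms of pelvic toxicity".
- **Table 1, population row.** The study population is women "who have completed pelvic radiotherapy (± chemotherapy". The statement is not limited to one cohort.

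The abstract defines the abbreviation as "Chronic pelvic toxicity induced by radiotherapy and/or chemotherapy (R/CIPT". R/CIPT is therefore a toxicity, and it can arise from CT alone.

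The between-group test in Section 5 (Statistical Approaches) is the Mann–Whitney U test, two-sided at 0.05, with 19 patients and 19 controls. The limitations paragraph relies on the single control sample for a first comparison of women with and without chronic R/CIPT. Its examples of recorded confounders are antibiotics and probiotics.

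**The concern.** A woman treated with CT only is eligible under criterion 1 and ineligible under Table 1, so the statements cannot all govern enrolment. For controls, the sentence that should decide the matter gives the name of the toxicity where a treatment should stand. The matching factors (age and tumour site) and the exclusion criteria do not remove a CT-only control either.

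The protocol's own background makes RT exposure relevant to the primary microbiological endpoint. Section 2(b) describes pelvic RT as irradiating the lower bowel directly, with changes that often persist. If every case was irradiated and some controls were not, a difference between the groups could reflect irradiation as well as toxicity. The Mann–Whitney test takes no covariates and cannot separate the two. Because there are only 19 controls, each sampled once, a badly composed control group would be hard to repair afterwards.

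**Working it through.** **Step 1: set the statements side by side.**

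| Place | Applies to | Pelvic RT required? | CT alone admitted? |
|---|---|---|---|
| Section 5, inclusion criterion 1 | all participants | no | yes |
| Section 5, primary cohort | toxicity cohort | yes | no |
| Section 5, control cohort | controls | unclear (names the toxicity) | unclear |
| Table 1, population row | not limited to one cohort | yes | no |

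The outcome depends on which statement governs:

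- Table 1 governs: no CT-only woman enters either cohort, and there is no imbalance from this source.
- Criterion 1 governs both cohorts: CT-only women can enter both, since the additional criterion for the ozone group asks only for chronic R/CIPT.
- The cohort definition governs cases and criterion 1 governs controls: CT-only women can enter the control group only. This is the reading that confounds the comparison.

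**Step 2: sample size.** 19 + 19 = 38, as stated. The article gives no power calculation, effect size or SD to reproduce.

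**Step 3: possible size under the third reading.** Inputs from the article are n = 19 per group and a two-sided Mann–Whitney U test at 0.05. Two inputs are not in the article and are assumed:

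- k, the number of CT-only controls out of 19;
- d, the difference in the outcome between irradiated (with or without CT) and CT-only women, in SD units.

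Spurious mean shift = (k/19) × d. For example, with k = 6 and d = 1.0 it is 6/19 × 1.0 = 0.316 SD; with k = 6 and d = 0.5 it is 0.158 SD.

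The rejection rate was simulated with 20,000 replicates per setting, normal outcomes with SD 1, no true toxicity effect, k controls shifted by d, and asymptotic p-values. Because the test is two-sided and the simulated outcome symmetric, the sign of d does not affect the rate.

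| k of 19 (share) | d = 0.5 | d = 0.8 | d = 1.0 |
|---|---|---|---|
| 0 (0%) | 4.7% | 4.6% | 4.6% |
| 2 (10.5%) | 4.7% | 5.2% | 5.3% |
| 4 (21.1%) | 5.4% | 6.6% | 7.3% |
| 6 (31.6%) | 6.6% | 9.2% | 11.9% |
| 10 (52.6%) | 10.9% | 19.8% | 28.4% |

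With pelvic RT required in both cohorts (k = 0), the rate sits at about the nominal level.

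**The case against.** The strongest reply is that the harm is conditional. Table 1, read literally, already excludes CT-only women, and criterion 1 applied evenly would admit them to both cohorts. The asymmetry needs a particular combination of readings. This stands: the mixing is possible, not certain. It does not remove the contradiction, because nothing in the article says which statement prevails.

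It can also be said that the control wording is a slip. Section 6 uses R/CIPT in the same way, apparently meaning the treatment. That is probably right, but if the phrase is read as RT/CT it still leaves open whether RT is mandatory.

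The control comparison is described as an initial one in a pilot that disclaims causal conclusions, and the confounder list is given by example. Both points are fair and limit the reach of the problem.

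A reader might infer two stronger conclusions that the article does not support:

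- **That the bias favours the hypothesis, because CT-only controls would have a healthier microbiota.** Section 2(c) presents the evidence for CT-induced dysbiosis as no weaker than that for RT, with loss of diversity and, for 5-FU, of short-chain fatty acid producers. The relevant quantity is RT (with or without CT) against CT alone, and the article gives neither its sign nor its size.
- **That controls also lack a time-since-RT requirement that the cases have.** The cases' three months is a duration of toxicity. No interval since RT is stated for either cohort, so there is no such mismatch to correct.

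**Conclusion.** The eligibility text contradicts itself on pelvic RT and should be reconciled before enrolment. The conclusion rests on the wording alone and needs no assumption.

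The statistical consequence is conditional. If CT-only women enter as controls while all cases are irradiated, the between-group microbiota comparison mixes toxicity with irradiation, in a direction and to a degree that the article does not allow one to determine. For assumed differences of 0.5 to 1.0 SD, inflation of the false-positive rate is negligible with 2 CT-only controls and small with 4. It becomes material with 6 to 10 if the difference is large. The top figure of 28% requires both a full 1 SD difference and more than half of the controls being CT-only, so it should not be read as the expected error rate.

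Only the toxicity-versus-control comparison is affected. The within-patient Wilcoxon comparison before and after ozone is not confounded by this.

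**What to change.** Make two wording changes:

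1. Change inclusion criterion 1 in Section 5 so that it requires completed pelvic RT, with or without CT, for both cohorts. This is what Table 1 already states and agrees with the toxicity-cohort definition.
2. Reword the control definition so that it names the treatment: women treated with pelvic RT, with or without CT, who have no pelvic toxicity symptoms.

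The cost is a minor amendment and a somewhat smaller pool from which to find 19 matched controls. The total stays at 38, and neither the tests nor the sampling schedule changes. Resolving the contradiction does not require further matching factors or a minimum interval since RT.

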Microbiological & Biomarker Endpoints: Primary Microbiological Endpoint: Changes in gut microbiota composition and diversity. Method: 16S rRNA gene sequencing (Illumina MiSeq platform) of stool samples. Analysis: Differential abundance of key taxa (e.g., Faecalibacterium, Roseburia, Akkermansia vs. Proteobacteria), and alpha/beta-diversity indices. Biomarker Endpoints: Serum samples will be cryopreserved at −80 °C in a registered biobank for subsequent batch analysis of inflammatory cytokines and oxidative stress markers.

Clinical Endpoints: Primary Clinical Endpoint: Pelvic and gynecological toxicity grade measured by: (1) CTCAE v5.0 scale, and (2) EORTC QLQ-CX24 module (cervical cancer-specific). Secondary Clinical Endpoints: (1) Quality of Life (QoL) measured by: EORTC QLQ-C30 (for cancer patients) and EQ-5D-5L™ (for the general population), (2) Psychological Status: Hospital Anxiety and Depression Scale (HADS), and (3) serum inflammatory/oxidative stress biomarker analysis.

Methodology: Sampling Schedule, Assays, and Statistical Approaches. Study Design: Prospective, observational study. Sample Size: 38 patients (19 with toxicity and OT, 19 matched controls without toxicity). Sampling Schedule: (1) R/CIPT Group: Baseline (pre-ozone) and post-treatment (after the final ozone session). (2) Control Group: A single time point during a routine follow-up visit.

Assays: Microbiota: Stool samples for DNA extraction and 16S rRNA sequencing. Inflammatory cytokines and oxidative stress markers: serum samples. The researchers analyzing the stool and serum samples will be blinded regarding the sample’s group assignment (non-toxicity control, pre-ozone, post-ozone).

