The analysis of serum biomarkers will encompass a comprehensive panel to evaluate both oxidative stress and inflammatory status. 1. Oxidative Stress Biomarkers: The assessment will include global oxidative stress markers such as FRAP (Ferric Reducing Ability of Plasma), which measures antioxidant capacity; dROMs (Reactive Oxygen Metabolites), which determines the peroxidation potential; and BAP (Biological Antioxidant Potential). Specific molecular biomarkers will also be quantified, including the activity of the key antioxidant enzymes Superoxide Dismutase (SOD) and Catalase (CAT), the levels of reduced glutathione (GSH) as a critical cellular antioxidant, Advanced Oxidation Protein Products (AOPP) as a marker of protein damage, and ROOH (Total Hydroperoxides) to assess the primary oxidation products of lipids and other molecules. 2. Inflammatory Biomarkers: The inflammatory profile will be characterized by measuring a panel of Pro-inflammatory Cytokines: Tumor Necrosis Factor-alpha (TNF-α), Interleukin-6 (IL-6)**,** Interleukin-1 beta (IL-1β), and Interleukin-8 (IL-8/CXCL8)**.** Furthermore, systemic inflammation will be evaluated through established clinical markers: C-Reactive Protein (CRP) and VES (Erythrocyte Sedimentation Rate)**.**

Statistical Approaches: Primary Analysis: Non-parametric tests will be used due to the small sample size (Wilcoxon signed-rank for pre/post ozone, Mann–Whitney U for inter-group comparisons). Spearman correlations for microbiota-clinical parameter associations. All variables will be described as medians and quartiles 1–3 (percentiles 25–75%). *p*-values less than 0.05 will be considered significant, and all hypothesis tests will be conducted two-sided. Software: R (v4.5.0 or higher).

This study is the first to prospectively explore the novel hypothesis that the clinical benefits of rectal OT for chronic R/CIPT could be mediated, in part, through gut microbiota modulation. The proposed mechanistic pathway is: Ozone → Attenuation of local oxidative stress and inflammation (via Nrf2 activation and NF-κB inhibition) → Restoration of a healthy mucosal microenvironment → Promotion of commensal bacteria (e.g., SCFA producers) and suppression of pathobionts → Improved barrier function and reduced systemic inflammation → Clinical improvement in toxicity and Quality of Life.

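### CTCAE Grade ≥2 admits the ozone patients and the same scale is a primary endpoint; if the qualifying grade is also the baseline, grades are expected to fall on average without any ozone effect

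*Protocol article*

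**What the plan says.** All references are to the protocol article, section 5, unless stated.

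- **Entry.** The Study Population paragraph takes women who "present with chronic pelvic toxicity (≥3 months duration) rated as Grade ≥2". The additional criteria for the ozone group give the duration in one sentence and the grade in another: "A toxicity grade of 2 (moderate symptoms; limiting instrumental activities of daily living) or higher, as per the CTCAE v5.0".
- **Endpoint.** The first-listed primary clinical measure is on the same scale: "Primary Clinical Endpoint: Pelvic and gynecological toxicity grade measured by: (1) CTCAE v5.0 scale". The QLQ-CX24 module is the second measure.
- **Timing.** The sampling schedule reads "R/CIPT Group: Baseline (pre-ozone) and post-treatment (after the final ozone session" for the treated group and "Control Group: A single time point during a routine follow-up visit" for the others. No run-in, repeat baseline or separate qualifying assessment is described.
- **Comparator.** Controls are "treated with R/CIPT but without symptoms of pelvic toxicity".
- **Test.** "Wilcoxon signed-rank for pre/post ozone", two-sided at 0.05, in the 19 treated patients.
- **Limitations.** The closing paragraphs of section 5 concede that the observational design and 38 patients rule out firm causal conclusions, and that controls are seen once. They do not mention regression to the mean. Table 1 gives the clinical aim as evaluating ozone's effect on toxicity.

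**The concern.** When patients are chosen because a fluctuating measure lies above a cut-off, some are chosen at a moment when it is higher than usual for them. On re-measurement the group mean moves back toward its usual level whatever treatment was given. Here the cut-off and the outcome share a scale, the selection is one-sided, and nobody with untreated toxicity is followed. Controls have no toxicity and a single visit, so they cannot show the drift.

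At stake is the direction of error in a primary test. A general caution about causality does not tell the reader that this test leans toward the hoped-for result. The clinical change is also what the study correlates with microbiota change and would carry forward to a randomised trial.

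**Working it through.** **Inputs from the article.** Entry at CTCAE Grade ≥2; CTCAE grade as endpoint; one pre-ozone and one post-treatment point; n = 19; Wilcoxon signed-rank; two-sided 0.05 (2.5% in the improvement direction). The sample size (38 = 19 + 19) comes without effect size, SD or power, so there is no planned figure to reproduce.

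**Assumed, because the article gives none of it.** Reliability r (the correlation of underlying severity between two gradings) of 0.9, 0.8 or 0.7. Share q of the referred pool at Grade ≥2 of 30, 50, 80, 90 or 95%. Grades 2/3/4 among those admitted of 70/25/5%, so the mean at entry is 2×0.70 + 3×0.25 + 4×0.05 = 2.35. The rest of the pool is split equally between Grades 0 and 1.

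**Step 1: direction, in closed form.** For normally distributed severity cut at c = Φ⁻¹(1−q), the expected change on re-measurement with no treatment effect is −(1−r)·φ(c)/q, in SD units. At r = 0.8:
- q = 30%: 0.2 × 0.348/0.30 = a fall of 0.23
- q = 50%: 0.2 × 0.399/0.50 = 0.16
- q = 80%: 0.2 × 0.280/0.80 = 0.07
- q = 90%: 0.2 × 0.175/0.90 = 0.04
- q = 95%: 0.2 × 0.103/0.95 = 0.02

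The change is negative whenever r < 1 and zero at r = 1. It shrinks as the cut-off excludes fewer of the pool.

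**Step 2: the planned test with no ozone effect.** Severity is cut into Grades 0 to 4, patients are admitted at Grade ≥2 with that grade as baseline, and 19 are re-graded and tested (normal approximation, zeros dropped; 10,000 simulated studies per cell).

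| q | Mean change in grade, r = 0.9 / 0.8 / 0.7 | False significant improvement, r = 0.9 / 0.8 / 0.7 |
|---|---|---|
| 30% | −0.217 / −0.350 / −0.482 | 25.7 / 40.9 / 56.6% |
| 50% | −0.154 / −0.252 / −0.344 | 16.1 / 24.5 / 34.2% |
| 80% | −0.073 / −0.116 / −0.151 | 6.6 / 7.9 / 10.8% |
| 90% | −0.043 / −0.065 / −0.083 | 3.6 / 5.0 / 5.3% |
| 95% | −0.024 / −0.036 / −0.045 | 2.5 / 3.6 / 3.9% |

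Simulation error is about one percentage point or less, so the ranges quoted elsewhere are rounded.

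**Step 3: movement in both directions.** At r = 0.8, from q = 30% to q = 95%, 43% down to 14% of patients improve by chance and 13% down to 12% worsen.

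**Step 4: with a baseline not used for selection.** If fluctuation at referral and at baseline is independent, the mean change is 0.00 and false improvement is about 2% in every cell. If the fluctuation carries over from referral to baseline with correlation 0.5, it is about 2 to 12%.

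**Step 5: requiring a second qualifying grade instead.** If both gradings must be ≥2 and the second is the baseline, false improvement is still 4.5 to 28.1% (q = 30 to 80%, r = 0.7 to 0.9). The gain comes from not selecting on the baseline, not from grading twice.

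**The case against.** **The referred pool may be mostly at Grade ≥2.** Section 5 says these patients are usually referred because symptoms resist conventional treatment. The threshold may then exclude few, and the bias is small: at q = 95% it is close to nominal. This stands, and it is why no single size can be claimed. A reader who looks only at the 30 to 50% rows might infer that a false positive is likely; the documents do not support that.

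**The toxicity is chronic.** The Study Population wording ties duration and grade together, which favours persistent disease and high reliability. The inclusion criteria separate the two, so a sustained Grade ≥2 is not clearly required, and referral at a bad time works the other way. Chronicity makes the bias smaller without removing it.

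**The shared assessment is not stated.** The only timing given is a sampling schedule, and Table 1 attaches it to stool and serum. An earlier referral grade may exist, and a condensed article may leave the visit schedule to the full protocol. This stands: the point is conditional on the qualifying grade being the baseline.

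**Causal limits are already conceded.** They are, and the study is presented as a pilot for a sham-controlled trial. The concession names no direction of bias, however. It defends the single control visit for comparing patients with and without toxicity, which is a different comparison from the pre/post test.

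**The other measure is not selected on.** QLQ-CX24 is affected only indirectly. This also stands.

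**Conclusion.** The point holds in a conditional form. The shared scale, the one-sided entry, the single listed pre-ozone point and the uncontrolled pre/post test in 19 patients are all in the text. If the qualifying grade is the baseline, the expected change without an ozone effect is downward unless grades are perfectly stable.

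The size rests entirely on the assumed reliability and referral mix. It runs from negligible to more than twenty times the nominal 2.5% (56.6/2.5 = 22.6).

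A reader might infer that grades must fall, or that chance can move them only down. Neither follows: the fall is an average, it vanishes with stable grades, and a Grade 2 patient can worsen. The change is worth making because it is cheap and the bias favours the hypothesis. Confidence in the size is limited.

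**What to change.** 1. Decide eligibility on the CTCAE grade documented at referral.
2. Take a separate CTCAE and QLQ-CX24 baseline just before the first ozone session, and do not use it to admit or exclude anyone.
3. Compute change from that baseline for every enrolled patient, including those then below Grade 2.
4. Report the referral-to-baseline change descriptively, with the length of the interval. That interval may differ from the 16 weeks of treatment, so it is not a control for it.
5. Name regression to the mean, with its direction, in the limitations in section 5.

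If the full protocol already separates the two gradings, stating so and adding items 4 and 5 is enough.

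**Cost.** One extra grading on a day the patient attends anyway, plus wording; treatment does not change. Some baselines will lie below Grade 2: in the independent case of step 4 about 2 to 37%, or 0.4 to 6.9 of 19 patients. The apparent improvement will be smaller.

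**What it does not do.** It removes the selection artefact fully only if fluctuation at referral has faded by baseline. Natural course and concurrent care would still need an untreated toxicity group.
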